### Objectives and hypotheses

The purpose of this study is to determine the efficacy of an online self-help program (deprexis®) for enhancing standard inpatient psychotherapeutic treatment at the end of the intervention. We hypothesize that the online self-help group has a lower BDI-II score at the end of the intervention (primary outcome). We further assume that this effect will already be measurable at termination of inpatient treatment and will be maintained up to the 3-month follow-up (secondary outcomes).

### Outcomes

As the primary endpoint, we defined reduction of BDI-II score in the intervention group (treatment as usual + deprexis®) compared to the control group (treatment as usual + online information) at T2 (end of intervention).

Key secondary endpoint(s):Reduction of BDI-II score at dischargeReduction of BDI-II score at 3-month follow-upReduction of depression (PHQ-9) and anxiety (GAD-7)Reduction of dysfunctional depression related cognitions (DAS)Improved self-esteem (RSE)Improved quality of life (EUROHIS-QOL)Therapeutic alliance (patient and therapist rating, HAQ)Acceptance and utilization of deprexis® and trial participationAcceptance and utilization of the information used in the control condition and trial participation Satisfaction with inpatient treatment and willingness to pay Improved working ability Remission from depression

Predictors of outcome:Recurrent depression (medical history of depression, previous inpatient treatment of depression)Childhood trauma (CTQ)Degree of structural deficits (OPD-SQ)Utilization of other treatment after inpatient treatment

A history of emotional abuse as assessed with the CTQ has been linked to depression in several studies [31,32]. Structural deficits, especially personality disorders, may also constitute a risk for the manifestation or recurrence of depression [33]. Thus, childhood trauma and structural deficits have a moderating effect on the primary outcome.

### Sample size calculation

In order to determine treatment effects, effect sizes are computed. Effect sizes achieved by deprexis® have been in the range between d = 0.58 and d = 1.24 in various studies [8,21]. As we use deprexis® as an adjunct to inpatient psychotherapy, we assume the lowest effect achieved to date. Based on a conservative estimate of an effect size of d = 0.5, a power of 0.80 and an alpha error of 0.05, a sample of n = 64 patients per group is required (calculation by GPower vs. 3.1[34]). Based on a total sample of n = 240 patients, n = 120 in the intervention and in the control group, this sample size will still be reached even when the drop-out rate exceeds 40%. All statistical analyses are performed with SPSS Statistics 21 (IBM Deutschland GmbH, Ehningen, Germany).

### Randomization

The assignment of patients to the intervention and control groups is achieved by block-randomization at a ratio of 1:1. With the help of the computer software Research Randomizer [35], randomization will be conducted centrally by the Study Center of Mental Disorders as an independent institution.

### Statistical methods

For the primary outcome criteria, analysis of covariance will be used to compare BDI-II scores at the end of treatment between the intervention and control condition, with baseline scores of the BDI-II as covariates.

Intent-to-treat analyses with multiple imputations to replace missing data as well as completer analyses will be conducted.

For the secondary analyses, self-report questionnaires (BDI-II, PHQ-9, GAD-7, RSE, EUROHIS-QOL 8, DAS, WAI, HAQ) will also be analyzed by analysis of covariance All analyses will be conducted on a two-sided level of significance of 0.05. Descriptive statistics showing the measurements over time will be presented whenever appropriate. In order to define the percentage of remitted patients, the reliable change index [36] will be computed. Patients with a post-treatment depression score in BDI-II below the cut-off of 13 and a reliable change regarding the reliable change index will be considered as remitted. Additionally, serious adverse events and drop-outs will be analyzed descriptively.

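### The primary ANCOVA is valid but adjusts only for baseline BDI-II, although the protocol names and collects further baseline predictors; adding them is a modest, nearly free gain in precision

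*Protocol article*

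**What the plan says.** All places are in the Methods of the protocol article unless stated.

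- **Primary model (Statistical methods).** BDI-II at the end of treatment is compared between arms by ANCOVA, "with baseline scores of the BDI-II as covariates". No further covariate is named. Multiple imputation is planned for the intention-to-treat analysis.
- **Named predictors (Outcomes).** A separate list of predictors of outcome gives recurrent depression ("medical history of depression, previous inpatient treatment of depression"), childhood trauma by CTQ, structural deficits by OPD-SQ, and use of other treatment after the inpatient stay. As rationale, the text links emotional abuse to depression and says that structural deficits "may also constitute a risk for the manifestation or recurrence of depression". It then describes trauma and structural deficits as moderators of the primary outcome.
- **Timing (Assessment, Table 1).** CTQ and OPD-SQ are marked at T0 only. The baseline BDI-II is the screening score. Treatment utilisation is marked at T3 only. Depression history has no row of its own.
- **Control of utilisation (Discussion).** The text says that outpatient psychotherapy after discharge will be assessed and controlled.
- **Allocation (Randomization).** "block-randomization at a ratio of 1:1"; no stratification factor is mentioned.
- **Power (Sample size calculation).** "Based on a conservative estimate of an effect size of d = 0.5", with "a power of 0.80 and an alpha error of 0.05", "a sample of n = 64 patients per group is required". The planned 120 per arm are said to leave enough patients even with more than 40% drop-out.

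**The concern.** The sponsor expects three baseline characteristics to predict outcome and collects two of them on dedicated scales at T0. Depression history, the third, exists before randomisation by its nature. None of the three has a role in the primary model, so whatever they explain beyond baseline BDI-II stays in the error term of the primary test.

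The only other variable that the article says it will control is outpatient treatment after discharge. That variable arises after randomisation and may itself be affected by the intervention, so adjusting the treatment comparison for it can bias the estimate. As written, the safe candidates have no adjustment role, while an unsafe one is said to be controlled.

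At stake is a somewhat wider confidence interval than the collected data would allow. It matters most if drop-out brings the trial down towards the 64 per arm that the plan tolerates.

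**Working it through.** **Inputs from the article.** d = 0.5, power 0.80, alpha 0.05, 64 per group required, 120 per arm randomised, drop-out of 40% or more tolerated. Sidedness comes from Statistical methods: "All analyses will be conducted on a two-sided level of significance of 0.05".

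**Assumed inputs, not in the article.** The correlation ρ between baseline BDI-II and BDI-II at T2 is taken as 0.3, 0.4 or 0.5. R² is the share of the variance remaining after baseline BDI-II that the three added predictors explain; it is taken as 0.02, 0.05 or 0.10.

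**Step 1: the plan's own figure.** A two-sided two-sample t-test (noncentral t, df = 2n − 2, noncentrality d·√(n/2)) gives power 0.795 at n = 63 and 0.801 at n = 64. The stated 64 per group reproduces.

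**Step 2: drop-out.** 40% drop-out leaves 120 × 0.6 = 72 per arm. The floor of 64 is reached at 1 − 64/120 = 46.7%. Unadjusted power is 0.801 at 64, 0.846 at 72 and 0.971 at 120 per arm. The target of 0.80 is therefore met without any covariate.

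**Step 3: effect of the added covariates on the standard error.** Residual variance is multiplied by (1 − R²), so the standard error falls by 1 − √(1 − R²), and the equivalent gain in patients is 1/(1 − R²) − 1.

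| Added R² | Standard error lower by | Equivalent extra patients |
|---|---|---|
| 0.02 | 1.0% | 2.0% |
| 0.05 | 2.5% | 5.3% |
| 0.10 | 5.1% | 11.1% |

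**Step 4: power at d = 0.5 with 64 per arm.** The effective effect size is 0.5/√[(1 − ρ²)(1 − R²)]. One degree of freedom goes to baseline BDI-II (df = 125) and three more to the added predictors (df = 122). Example with ρ = 0.4 and R² = 0.05: 0.5/√(0.84 × 0.95) = 0.560, noncentrality 0.560 × √32 = 3.17, power 0.881.

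| ρ | BDI-II only | R² = 0.02 | R² = 0.05 | R² = 0.10 |
|---|---|---|---|---|
| 0.3 | 0.837 | 0.844 | 0.855 | 0.873 |
| 0.4 | 0.865 | 0.871 | 0.881 | 0.897 |
| 0.5 | 0.900 | 0.905 | 0.914 | 0.927 |

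Over this grid the gain runs from 0.5 points (ρ = 0.5, R² = 0.02) to 3.6 points (ρ = 0.3, R² = 0.10). At 72 per arm with ρ = 0.5, power goes from 0.931 to 0.935, 0.942 or 0.952.

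**Step 5: chance imbalance.** The difference between arms in a standardised covariate has standard deviation √(2/n): 0.129 at 120 per arm and 0.177 at 64. With R² = 0.05 for that covariate, an imbalance of 0.177 shifts the estimate by √0.05 × 0.177 = 0.04 residual standard deviations. The standard error already allows for this variation. It is the same residual variance as in Step 3 and not a second loss.

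**The case against.** The strongest reply is that nothing here is wrong. ANCOVA on the baseline value of the outcome is valid under randomisation, usually contains the strongest single prognostic variable, and exceeds the design power for any useful ρ. This stands, and it is why the point is an improvement and not a correction.

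The size of the gain cannot be derived from the article, and at R² near 0.02 it is negligible. That also stands. The stated rationale concerns the risk and recurrence of depression and moderation; it does not show that the variables explain T2 scores beyond baseline BDI-II. Even so, the article does call them predictors of outcome, and a moderation model would contain their main effects anyway.

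A reader might infer more than the article supports:

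- **That balance is given up.** Chance imbalance neither biases the estimate nor inflates the type I error rate, and adjustment does not create balance.
- **That randomisation is unstratified.** The Randomization section mentions blocks and no strata, but silence in a condensed article does not establish this.
- **That PHQ-9 belongs in the model for the same reason.** It is measured at T0, but it is listed as an outcome, is not a named predictor, and overlaps with BDI-II. It is optional.

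One practical objection has weight. The article does not show that the T0 questionnaires are completed before allocation: they are administered online, and access codes are mentioned only after randomisation. Restricting adjustment to values recorded before allocation or before first programme access meets this.

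**Conclusion.** The point holds as a low-priority, nearly free improvement. The stated primary model is sound, but it makes no use of three baseline variables that the protocol itself names as predictors.

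With an assumed added R² of 0.02–0.10, prespecified adjustment makes the standard error about 1–5% smaller and adds roughly 1–3 power points at d = 0.5 with 64 per arm. At the full 120 per arm, power is already so high that the benefit is mainly a slightly narrower interval. These sizes depend on the assumed R² and, for power, on the assumed ρ. The direction of the recommendation does not depend on the exact values, since three degrees of freedom cost almost nothing at 128 to 240 patients.

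The clearer part of the point concerns treatment utilisation: it should not enter the adjustment of the treatment comparison.

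**What to change.** Before unblinded analysis, prespecify the primary ANCOVA of BDI-II at T2 with arm, screening BDI-II, recurrent depression, CTQ total and OPD-SQ total, all as main effects. In addition:

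- Use only values recorded before allocation or before first access to the online programme.
- State how recurrent depression is coded, since the article gives two components (history and previous inpatient treatment).
- Put the same variables in the multiple imputation model, which also deals with occasional missing covariate values.
- Keep the model with BDI-II alone as a supportive analysis.
- Exclude treatment utilisation after discharge from the adjustment, and say what the Discussion means by controlling it, for example a descriptive or separate exploratory analysis.
- Keep any test of moderation by CTQ or OPD-SQ separate from this main-effect adjustment.

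The cost is a few sentences in the analysis plan and three degrees of freedom. CTQ and OPD-SQ are already scheduled; the source of the depression history should be confirmed. Because enrolment began on 1 July 2014, the change should be documented as a dated amendment made without knowledge of outcomes by arm.

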## Methods

### Participants

At admission to inpatient psychotherapy, patients are informed about the study. Those eligible are inpatients aged 18 to 65 years who have private internet access, sufficient German language proficiency, a score in the clinical range (>13) of the Beck Depression Inventory-II (BDI-II) [19] and a clinical diagnosis of depression (International Statistical Classification of Diseases and Related Health Problems, 10th revision (ICD-10), codes F32.x, F33.x, F34.1, F43.2), as assessed by the individual therapist of the patient. Those excluded are patients suffering from psychosis, current alcohol or drug addictions, borderline, antisocial, schizoid and schizotypal personality disorders, anorexia nervosa, lifetime diagnoses of schizophrenia, schizoaffective, bipolar or organic mental disorder.

The study assistant screens every patient at intake who fulfils the BDI-II criteria in the standard intake assessment and who is diagnosed with a depressive disorder by his or her therapist regarding inclusion and exclusion criteria.

Data for patients who are eligible for participation and have given written informed consent are coded, and patients are randomized by the study center. Study information is given to the patients by a study assistant. They are provided with their access codes for the online self-help program or the online platform of the control condition and receive a short introduction to their respective treatment condition.

The Study Center of Mental Disorders at the University Medical Center of the Johannes Gutenberg-University Mainz is responsible for storing personal data and randomizing participants. Administration of the internet-platform and allocation of the weekly information text in the control condition are managed by psychologists of the Department of Psychosomatic Medicine and Psychotherapy of the University Medical Center Mainz.

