### Assessment

Assessments are conducted at the beginning (T0) and the end (T1) of inpatient treatment, at the end (T2) of intervention and 6 months after randomization (T3; Figure 1). Screening is based on the BDI-II [19], a reliable and valid 21-item self-report scale of depression, during the past 2 weeks, together with ICD-10 diagnoses made by the individual therapist. At T0 patient characteristics (for example, education, employment, family status) will be taken from the basic documentation of the clinic. In addition to the BDI-II, the reliable and valid Patient Health Questionnaire (PHQ-9) is used to assess depression [22] along with the Generalized Anxiety Screener (GAD-7) [23]. Other self-report questionnaires assess self-esteem (Rosenberg Self-Esteem Scale, RSE) [24], quality of life (European Health Interview Survey Quality of Life 8 Item Index, EUROHIS-QOL 8) [25] and dysfunctional depression-related cognitions (Dysfunctional Attitude Scale, DAS) [26]. We further assess childhood trauma with the Childhood Trauma Questionnaire (CTQ) [27]. The Work Ability Index (WAI) [28] questions current work ability in relation to physical and mental job demands, and prognosis for the forthcoming 2 years. Structural psychological deficits are assessed by the short form of the OPD Structure Questionnaire (OPD-SQ) [29], and the therapeutic alliance by the Helping Alliance Questionnaire (HAQ) [30], with a patient as well as a therapist rating.

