**Figure 1 Fig1:**
[figure not shown]
**Study design and time points of assessment.** TAU, treatment as usual.

At discharge (T1) and follow-up (T3) subjects fill out the BDI-II, PHQ-9, GAD-7, RSE, EUROHIS-QOL 8, WAI and the DAS. At discharge, we furthermore assess the HAQ, satisfaction with inpatient treatment, and acceptance of and satisfaction with deprexis® (intervention) or the online information (control condition). At the end of the intervention (T2) subjects fill out the BDI-II and a questionnaire concerning acceptance and satisfaction analogous to T1, including items assessing willingness to pay for the intervention (deprexis®). In addition, utilization of other treatments after the end of inpatient treatment will be measured at T3 (Table 1).

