In our study design, it did not seem feasible to keep therapists blind to the intervention that patients received, as this may interfere with an intensive psychotherapy process. In order to reduce potential bias (for example, therapist expectation), we used patient self-reported depression score as the main outcome. Inpatient treatment is psychodynamically oriented, whereas the online program constitutes a blend of modules from different psychotherapeutic, mostly cognitive-behavioral, traditions. We do not train therapists in the interventions delivered in the online program in order to keep it as an adjunct. In order to deal with the concern of therapists about potential effects of the online program participation on the inpatient treatment process, we assess helping alliance both from the perspective of the therapist and the patient at treatment termination in order to make sure that participation in the behaviorally oriented online program does not interfere with the therapeutic relationship which is considered to be of paramount importance for outcome in psychodynamic treatment [38]. We also ask therapists specifically about their experience. As we surmise that a substantial part of the sample will continue or enter new outpatient psychotherapy in the first months after inpatient treatment [39], we also assess and control this variable.

We chose a commercially available program which has been thoroughly tested and empirically validated. Costs of the online self-help program are being covered by the hospital for this study, as online interventions are currently not reimbursed by the German health insurances. In order to answer the question if this approach is feasible without external funding, we will ask patients if they would be willing to pay for the online self-help program and to what extent.

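### The Protocol article lists the HAQ as a self-report scale for ANCOVA, but one of its two forms is completed by the therapist; modelling the rater would sharpen the check for interference with the alliance

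*Protocol article*

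**What the plan says.** The Statistical methods section of the Protocol article names one method for the secondary scales: "self-report questionnaires (BDI-II, PHQ-9, GAD-7, RSE, EUROHIS-QOL 8, DAS, WAI, HAQ) will also be analyzed by analysis of covariance". It does not separate the two HAQ forms and mentions no therapist term.

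Other sections show that there are two forms. The Assessment section describes the HAQ "with a patient as well as a therapist rating". The Outcomes section counts both forms among the key secondary endpoints. The Discussion states that "we assess helping alliance both from the perspective of the therapist and the patient at treatment termination", in order to make sure that taking part in the program "does not interfere with the therapeutic relationship".

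Three design features bear on the analysis:

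- **Rater.** Each patient has an individual therapist. The Participants section has the qualifying diagnosis made before randomisation, "as assessed by the individual therapist of the patient".
- **Timing.** The text under Figure 1 says "At discharge, we furthermore assess the HAQ", and Table 1 marks the HAQ at discharge only.
- **Allocation.** The Randomization section specifies "block-randomization at a ratio of 1:1", with no mention of stratification by therapist.

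**The concern.** A therapist who completes the form for several patients brings a personal standard to all of them. Ratings from the same therapist are then correlated, which does not apply in this way to scales that each patient completes once about himself or herself. As the HAQ is not measured at baseline, no earlier HAQ value can serve as a covariate and absorb these differences. A model without the therapist leaves them in the residual variance.

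The purpose of the measure makes this relevant. The rating is meant to reassure that the program does no harm to the alliance. For such a check an imprecise estimate favours the reassuring answer, because a real worsening is more easily missed. The therapist is known before randomisation and is therefore a legitimate factor to model.

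**Working it through.** **The plan's own figure.** The Sample size section gives 64 per group for d = 0.5, power 0.80 and alpha 0.05. The exact two-sided t calculation gives 64 (power 0.8015), so the figure reproduces. With 120 randomised per arm, 64 remain at a drop-out of up to (120 - 64)/120 = 46.7%, which agrees with the statement that more than 40% can be tolerated. Both figures concern the BDI-II; the article gives none for the HAQ.

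**Inputs.** From the article: 120 per arm, 1:1 allocation of individual patients in blocks, two-sided 0.05. Assumed, because the article does not give them: block size 4, 10 to 40 therapists, and a share of rating variance between therapists (ICC) of 0 to 0.3. The worsening to be detected is set at 0.3 SD.

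**Without a therapist term.** SE = SD × sqrt(2/n) = sqrt(2/120) = 0.129 SD. The 95% half-width is about 0.25 SD and the power for 0.3 SD is 63.9%.

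**Upper limit of the gain.** If all between-therapist variance is removed, SE = sqrt(2/120) × sqrt(1 - ICC):

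| ICC | sqrt(1 - ICC) | SE (SD) | Ideal power at 0.3 SD |
|---|---|---|---|
| 0 | 1.000 | 0.129 | 63.9% |
| 0.1 | 0.949 | 0.1225 | 68.4% |
| 0.2 | 0.894 | 0.1155 | 73.5% |
| 0.3 | 0.837 | 0.108 | 79.0% |

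**Gain with the model proposed here.** The ideal is not fully reached because the arms are not exactly balanced within each therapist. Simulation of a random-intercept model (REML, 240 patients, 10 to 40 therapists) gave, for 0.3 SD:

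| ICC | No therapist term | Random intercept |
|---|---|---|
| 0 | about 64% | no meaningful loss |
| 0.1 | about 64% | 66-68% |
| 0.2 | about 64% | 70-73% |
| 0.3 | about 64% | 75-77% |

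Separate runs vary by about one percentage point.

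**Validity of the plain analysis.** If therapists differ only in their rating level, the simulated type I error without a therapist term was 0.046 to 0.062, with no trend in the ICC. With the random intercept it stayed near 5%.

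**Therapist-specific program effects.** Suppose the program's effect on the rating differs between therapists with SD 0.3 (assumed), averages zero across therapists in general, and there are 15 of them. The plain model then rejects a true null about 9% of the time. With the random intercept alone the rate is 9-11%. The intercept does not cure this, because the variation in the arm effect is still not modelled.

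**The case against.** **Silence in a condensed article.** The article names a family of methods for eight scales in one sentence. A therapist term may be in a fuller plan that is not shown. This stands as a limit: the absence of a rater term would be no finding by itself. What the article does state is that the HAQ is a self-report questionnaire, and that does not fit its therapist form.

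**The sentence may cover only the patient form.** Read literally, it may, and this cannot be settled from the text. In that case the article names no method for the therapist half of a key secondary endpoint. Either reading calls for a clarification.

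**Everything quantitative is assumed.** This also stands. The article gives no number of therapists, no patients per therapist and no ICC. At an ICC of 0.1 the gain is only a few percentage points.

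**Adjustment can cost power.** This is true of fixed therapist effects: with 40 therapists and an ICC of 0.1, simulated power fell from 64.6% to 59.9%. It does not apply to the random intercept, which showed no meaningful loss even at an ICC of 0.

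**Stronger readings that a reader might infer.**

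- That ignoring the therapist invalidates the test. Patients are randomised individually, so most therapists would have patients in both arms, and the error rate stays near 5% unless the program's effect itself varies by therapist.
- That the adjustment is worth 43% more patients at an ICC of 0.3, since 1/(1 - 0.3) = 1.43. That is an idealised ceiling which the simulated gain does not reach.
- That the patient-rated HAQ needs the same model. Each patient rates once, so the argument about lenient and strict raters does not carry over, and no calculation supports it.

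**Conclusion.** The point holds as a minor improvement to one secondary endpoint. The self-report label does not fit the therapist form of the HAQ. If that form is analysed by an ANCOVA without a therapist term, the comparison is valid for the average effect but less precise than it could be.

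The size depends on how much therapists differ in their rating level: a few percentage points of power at an ICC of 0.1 and more than ten at 0.3, for a 0.3 SD difference with 120 patients per arm. This rests on assumed ICCs, on 10 to 40 therapists, and on the inference that therapists rate several patients, normally from both arms. If raters hardly differ, there is no gain.

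The caution about therapist-specific effects applies to the plain and the random-intercept model alike, and only if conclusions are meant to reach beyond the therapists in the trial. The primary BDI-II comparison is not affected.

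**What to change.** 1. In Statistical methods, name the two HAQ forms separately and state that the therapist form is not self-report.
2. Analyse the therapist-rated HAQ in a mixed model with arm as fixed effect and therapist as random intercept. Avoid fixed therapist effects if there are many therapists. As there is no baseline HAQ, name any covariate that is used.
3. Add a random arm-by-therapist term as a sensitivity analysis, because the intercept alone does not protect against program effects that differ between therapists.
4. Leave the primary BDI-II ANCOVA and the analysis of the patient-rated HAQ as they are.

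The cost is a few lines of analysis text and a coded therapist identifier in the data set. No further data are needed from patients.

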**Table 1 Tab1:** **Schematic overview of frequency and scope of the study visits**

	**Screening**	**Pretreatment**	**Discharge**	**End of Intervention**	**Follow-up**
Study visits		T0	T1	T2	T3
Written informed consent	X				
Screening questions	X				
BDI-II	X		X	X	X
GAD-7		X	X		X
PHQ-9		X	X		X
RSE		X	X		X
EUROHIS-QOL 8		X	X		X
DAS		X	X		X
CTQ		X			
WAI		X	X		X
OPD-SQ		X			
HAQ			X		
Satisfaction with intervention			X	X	
Utilization of other treatment					X
BADO		X	X		
Willingness to pay				X	
Adverse events		continuously	X	X	

BADO, basic documentation; BDI-II, Beck Depression Inventory-II; CTQ, Childhood Trauma Questionnaire; DAS, Dysfunctional Attitude Scale; EUROHIS-QOL 8, European Health Interview Survey Quality of Life 8 Item Index; GAD, Generalized Anxiety Screener; HAQ, Helping Alliance Questionnaire; OPD-SQ, OPD Structure Questionnaire; PHQ, Patient Health Questionnaire; RSE, Rosenberg Self-Esteem Scale; WAI, Work Ability Index.

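### The stated safety analysis covers serious adverse events and drop-outs, although Table 1 collects adverse events without that limit, and the reliable change index is not planned for counting patients who worsen

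*Protocol article*

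**What the plan says.** **Collection.** Table 1 of the protocol article carries a row headed "Adverse events". It is marked as continuous under T0, has an entry at T1 and at T2, and has none at T3. The label carries no restriction to serious events.

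**Safety analysis.** Statistical methods contains one sentence on safety: "Additionally, serious adverse events and drop-outs will be analyzed descriptively". The endpoint list under Outcomes ends with "Remission from depression" and includes no adverse event or deterioration outcome.

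**Reliable change index.** Its stated purpose is remission: "In order to define the percentage of remitted patients, the reliable change index [36] will be computed". The remission rule is built on "Patients with a post-treatment depression score in BDI-II below the cut-off of 13 and a reliable change regarding the reliable change index". No matching category is defined for change in the unfavourable direction.

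**Related provisions.** Statistical methods also says "Descriptive statistics showing the measurements over time will be presented whenever appropriate". The Discussion notes therapists' concern about "potential effects of the online program participation on the inpatient treatment process". It answers that concern with patient and therapist ratings of the helping alliance, to check that the program "does not interfere with the therapeutic relationship".

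**The concern.** The article does not leave the safety analysis open for a fuller document to settle. It states the analysis and qualifies it with the word serious. An analyst who follows that sentence produces less than Table 1 collects.

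The same holds for worsening. The index and the BDI-II scores needed to count patients who become reliably worse are already in the plan, but only the favourable direction is named.

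This matters because the intervention is an unguided program added to inpatient psychotherapy and continued after discharge. A plausible harm in that setting is a worsening of depression that does not meet a definition of seriousness. A comparison of means does not answer that question, because a better group mean can coexist with more patients who deteriorate. Without a count, the report can say less about harm than the data allow. If the decision to add such a table is left until results are known, it is open to selective reporting.

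**Working it through.** The disputed point is textual, so steps 1 to 3 set the passages side by side. Steps 4 to 6 give the relevant figures.

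**1. Adverse events.** Collected (Table 1): adverse events, no seriousness limit, T0 to T2. Committed to analysis (Statistical methods): serious adverse events and drop-outs. No section names an analysis of non-serious events.

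**2. Reliable worsening.** The BDI-II is scheduled at screening, T1, T2 and T3 (Table 1). The screening score can serve as the starting value, so reliable change can be computed at three later time points. The stated output is the percentage remitted. The percentage reliably worse is not named.

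**3. What the plan does cover.**
- Mean BDI-II is compared between arms by analysis of covariance, two-sided, at T2 (primary) and at T1 and T3 (secondary). Worsening of a group mean would show.
- The helping alliance is a listed secondary endpoint and is also analysed by covariance, but Table 1 schedules it at T1 only. The program is accessible for 12 weeks from first login (Intervention), and the Background speaks of inpatient treatment of 4 to 8 weeks. If login is near admission (an assumption), 12 − 8 = 4 to 12 − 4 = 8 weeks of access fall after the alliance rating.

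For those weeks the main information on harm is the adverse event row and the BDI-II.

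**4. The plan's own sample size.** Inputs from Sample size calculation: d = 0.5, power 0.80, alpha 0.05 (two-sided per Statistical methods), 1:1 allocation.
- Normal approximation: n = 2(1.96 + 0.8416)² / 0.5² = 62.8, so 63 per group.
- Two-sample t-test: 63.77, so 64 per group, with power 0.801 at n = 64. This reproduces the stated 64.
- Drop-out: 120 × 0.60 = 72, which exceeds 64. The break-even loss is 1 − 64/120 = 46.7%.

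Nothing in this point changes these figures.

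**5. What serious events alone can show.** With zero events in n patients, the one-sided 95% upper bound is 1 − 0.05^(1/n):

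| n per arm | Upper bound |
|---|---|
| 120 | 2.5% |
| 72 (40% loss) | 4.1% |
| 64 | 4.6% |

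These bounds apply to serious events and say nothing about non-serious ones.

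**6. Whether a count of worsening is feasible.** The article gives no SD or reliability for the BDI-II, so the following values are assumptions.
- Threshold: 1.96 × SD × √(2(1 − r)). With SD 8 and r = 0.93 it is 5.9 points; with SD 12 and r = 0.80 it is 14.9 points. The same threshold applies in either direction.
- If 3% to 10% of 120 patients in an arm worsened reliably, that is 3.6 to 12 patients. The 95% half-width, 1.96 × √(p(1 − p)/120), is 3.1 to 5.4 points.
- For an illustrative split of 5% against 10% (6 against 12 patients), the half-width for the difference is 1.96 × √(0.05 × 0.95/120 + 0.10 × 0.90/120) = 6.6 points. That is wider than the 5-point difference.

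So the count can be made from planned data, but it supports description, not a firm comparison.

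**The case against.** The strongest reply is that this is a condensed article. Detailed adverse event tables and a deterioration analysis are commonly left to a full protocol or analysis plan, which is not shown. The safety sentence opens with an additive word and excludes nothing. The Table 1 label is bare and neither term is defined, so the row may be shorthand for serious events. Using the reliable change index for remission is not an error. The Discussion's concern is also met by a dedicated measure: the alliance is rated by both patient and therapist, and therapists are asked about their experience.

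Much of this stands. A reader might infer that the non-serious events will be thrown away, or that patients who get worse cannot be seen in the results. The documents support neither inference. No sentence excludes these outcomes, and mean worsening, drop-outs and the alliance are all to be analysed. Nor are adverse events recorded over the whole study, since the row has no T3 entry. The article does not announce a claim that the program is harmless, and an imprecise table of worsening could not establish one.

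What does not fall away is the mismatch of scope. The article is not silent on safety: it states an analysis, and as worded that analysis is narrower than the table of assessments. If the row was meant as serious events only, the two places still need the same wording. The deterioration count is the weaker half of the point. It is an inexpensive addition, not the correction of an error.

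**Conclusion.** The point holds as a minor reporting matter. Statistical methods commits to serious adverse events and drop-outs, while Table 1 records adverse events without that limit from T0 to T2. The reliable change index is named only for remission, so the proportion reliably worse is not a planned output, although the BDI-II is held at T1, T2 and T3.

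The conclusion rests on reading the Table 1 label at face value and on the article alone; a fuller document could already resolve it. The documents give no figure from which to estimate how many patients would worsen, so no size is claimed for that. The rates in the working are illustrations of precision. The primary test, the 64 per group and the drop-out allowance are untouched.

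**What to change.** Amend the safety sentence in Statistical methods along these lines: *All recorded adverse events, serious and non-serious, and drop-outs will be tabulated by arm. The number and percentage of patients with reliable deterioration on the BDI-II (same reliable change index, opposite direction) will be reported descriptively by arm at T1, T2 and T3.* If the Table 1 row was intended to mean serious events only, say so there, so that the two places agree.

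The change should be made before outcome results by arm are seen. It costs one or two descriptive tables from data already scheduled, with no extra assessment and no change to the primary analysis. The drawback is imprecision: the estimates should be labelled descriptive and should not be read as evidence that harm is absent.
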